**Perform post treatment assessment**

**Statistical Analysis**

**Participants:**

Inclusion criteria are as follows:

1. Age 18-50 years, who have been referred from the Dept. of Orthopaedic.
2. Patients must be diagnosed with an A3 extraarticular multi-fragmentary distal radial fracture type and treated conservatively with plaster cast immobilization and closed reduction.
3. Participants must accept and sign the Informed consent.
4. No previous history of wrist/ hand fracture, history of inflammatory arthritis, or any possible upper limb fracture.
5. Patients who are able to comprehend (Lyngcoln et al., 2005).

Exclusion criteria are as follows:

1. Participants who were treated for DRF reduction and/or fixation with some form of surgical intervention (e.g. external fixation, volar plate, and Kirschner wires).
2. Patients with Mini-Mental score less than 26 points on the examination.
3. After the removal of the immobilization, patients with immediate complications like malunion or non-union.
4. Patients with past trauma either in arms or hands that had impaired function.
5. Patients with inflammatory or non-inflammatory diseases and neurological disorder were excluded.

**Sample size consideration:** This is an experimental study with two-group design that examines the effect of leap motion control in distal radial fracture rehabilitation. Analysis of previous power using G*Power is used to determine the same size (Engel et al., 2019). 40 participants will be enrolled to the control group or experimental group and will be allocated accordingly (Maciel et al., 2005). The G*Power analysis followed the following terms for calculation of sample size which is graphical represented in figure 2.

**t tests** - Means: Difference between two independent means (two groups)

**Analysis:** A priori: Compute required sample size

**Input:** Tail(s) = One

Effect size d = 0.8

α err prob = 0.2

Power (1-β err prob) = 0.95

Allocation ratio N2/N1 = 1

**Output:** Non-centrality parameter δ = 2.5298221

Critical t = 0.8511828

Df = 38

Sample size group 1 = 20

Sample size group 2 = 20

Total sample size = 40

Actual power = 0.9531573

**Figure 2:** The calculation of sample size using G*Power analysis

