**Statistical analysis:** The SPSS latest version will be used to perform statistical analysis. To compare the group effect, two-way repeated measures ANOVA (analysis of variance) will be used. When ANOVA reveals a significant difference, student’s t test will be used to compare the changes within the group. Statistical significance is determined by a two-sided p value of less than 0.05. Mann-Whitney U, t-test or Fisher’s exact test will be used for comparing Groups at baseline and for comparing the primary and secondary outcomes between the groups at 6 weeks.

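### Two between-group analyses are named for each outcome and neither is made decisive; if either may be claimed, the false-positive chance per outcome is about 7–9%, not 5%

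*Protocol*

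**What the plan says.** The Statistical analysis paragraph of the protocol contains two between-group comparisons of the outcomes.

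- The first is the ANOVA: "To compare the group effect, two-way repeated measures ANOVA (analysis of variance) will be used". The paragraph does not mention a group-by-time term.
- The second comes at the end of the paragraph. A Mann-Whitney U, t or Fisher's exact test is to be used for baseline comparisons and also "for comparing the primary and secondary outcomes between the groups at 6 weeks".

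One threshold covers everything: "Statistical significance is determined by a two-sided p value of less than 0.05". The only conditional step is "When ANOVA reveals a significant difference, student’s t test will be used to compare the changes within the group". That step concerns changes within a group, so it does not make the 6-week between-group test depend on the ANOVA.

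The Sample size consideration paragraph uses a t-test calculation labelled "Difference between two independent means (two groups", with 20 patients in each group. Neither that paragraph nor the Power analysis paragraph says which of the two analyses the trial's conclusion will rest on.

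**The concern.** The two analyses put the same question to the same data, but they test different quantities. With one baseline and one post-treatment value, the ANOVA group effect compares the average of the two values. The group-by-time interaction compares the change. The 6-week test compares the post-treatment value alone. The three can give different answers in one trial, and each would meet the stated significance rule.

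Two things are at stake. If a claim may rest on whichever analysis is significant, the 0.05 level does not hold even for a single outcome. If the device truly works, whether the trial counts as positive can depend on which analysis is reported. Neither problem comes from having several outcomes: both would remain if DASH were the only one.

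**Working it through.** **Inputs from the protocol.** Two-sided 0.05 per test (Statistical analysis). 20 per group, 1:1 allocation and d = 0.8 (Sample size consideration). A baseline and a post-treatment assessment (flow chart).

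**Assumed.** Normal data with equal variances, and a correlation r of 0.3 to 0.7 between the baseline and 6-week values. The protocol gives no correlation.

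**Step 1: reproduce the protocol's figure.** The noncentrality is 0.8 × √(20/2) = 2.530. With 38 degrees of freedom and the one-sided level entered there ("α err prob = 0.2"), the critical t is 0.851 and the power 0.953, as printed. At the two-sided 0.05 of the analysis paragraph, the critical t is 2.024 and the power of the same t test is 69%. That difference in level is a separate matter. The 69% serves below as the reference for the 6-week t test.

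**Step 2: what each analysis tests.** Take unit variance at each visit and a true difference of 0.8 at 6 weeks only. The effect size each analysis sees is 0.8 divided by the standard deviation of the quantity tested. Power then follows from noncentrality = effect size × √10.

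| Analysis | SD of the quantity tested | Effect size, r = 0.3 / 0.5 / 0.7 | Power, two-sided 0.05 |
|---|---|---|---|
| ANOVA group effect (sum of visits) | √(2(1+r)) | 0.50 / 0.46 / 0.43 | 33% / 30% / 27% |
| ANOVA interaction (change) | √(2(1−r)) | 0.68 / 0.80 / 1.03 | 55% / 69% / 89% |
| 6-week t test | 1 | 0.80 | 69% |
| 6-week value adjusted for baseline (ANCOVA) | √(1−r²) | 0.84 / 0.92 / 1.12 | 73% / 81% / 93% |

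**Step 3: no true effect.** In simulated trials (40,000 to 100,000 per setting), each test alone rejects in about 5%. The chance that at least one of the counted tests gives p < 0.05 is:

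| Tests that may each support a claim | Chance, r = 0.3–0.7 |
|---|---|
| Group effect or 6-week t test | about 7–8% |
| Interaction or 6-week t test | about 9% |
| Both ANOVA terms or 6-week t test | about 11–12% |
| Both ANOVA terms, 6-week t test or Mann-Whitney | about 12% |

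The first row is the lowest because the group effect and the 6-week value are strongly correlated, at √((1+r)/2) = 0.81 to 0.92. For the interaction the correlation is √((1−r)/2) = 0.59 to 0.39, so there is more room for a second chance. Any two tests at 0.05 are bounded by 0.05 + 0.05 = 10%.

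Widening r to 0–0.9 gives 6.1–8.3% for the first row and 8.2–9.7% for the second. If a third visit is added, since the Follow up paragraph could be read that way, the first two rows become 7.1–8.1% and 8.8–9.4% (r = 0.3–0.7).

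**Step 4: true d = 0.8.** The group effect and the 6-week t test reach different conclusions in about 38–43% of simulated trials. The power gap alone forces at least 69 − 33 = 36 to 69 − 27 = 42 percentage points of disagreement, so it explains nearly all of it. The interaction and the 6-week t test disagree in about 30%.

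**The case against.** The strongest case on the other side has five parts.

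- **The decision rule is assumed.** The protocol sets a threshold for significance; it does not say that a significant result on any analysis is enough for a claim. This stands, and the false-positive figures are conditional on it.
- **The tests are fewer than they look.** The ANOVA is assigned to the group effect, so counting the interaction as well goes beyond the text. The list of 6-week tests is joined by *or* and includes Fisher's exact test, so it reads as a choice by type of data. This also stands. A reader might infer that the two named analyses give an 11–12% error rate. The documents do not support that: two tests cannot exceed 10%, and the higher figure needs both ANOVA terms to count as separate routes.
- **The sample size points to one test.** The calculation is a two-group t test, and the Power analysis paragraph ties adequate power to completing 6 weeks of follow-up. That favours the 6-week comparison but does not make it decisive, and the analysis paragraph names the ANOVA first.
- **A statistical analysis plan may rank the analyses.** It may, and for that reason the missing rule for t test versus Mann-Whitney is not held against the protocol. What remains is that the protocol itself sets two competing between-group tests side by side under one threshold.
- **The disagreement under a true effect mostly reflects the weak group effect.** Correct, as Step 4 shows. It still means that the conclusion depends on which named analysis is taken.

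**Conclusion.** The point holds in a limited form. The protocol names two between-group analyses of the same outcomes at two-sided 0.05 and does not say which one decides. If either may be claimed, the false-positive chance per outcome is about 7–8% or about 9%, depending on which ANOVA term is meant. The 11–12% range applies only if both ANOVA terms count together with the 6-week test, in one or both versions. These figures rest on normal data, a correlation of 0.3–0.7 that the protocol does not give, and a claim rule that it neither states nor excludes.

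The consequence under a true effect does not need that claim rule. At d = 0.8 the group effect has 27–33% power and the 6-week t test 69%, and they disagree in about 38–43% of trials. This should be corrected before the data are analysed.

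**What to change.** In the Statistical analysis paragraph, name one deciding contrast for each outcome: the between-group difference at the 6-week assessment, adjusted for the baseline value of that outcome (ANCOVA), tested at two-sided 0.05 and reported with its 95% confidence interval. State that the repeated-measures ANOVA, through its group-by-time term, and the Mann-Whitney test are sensitivity analyses that cannot by themselves support a claim.

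This takes two or three sentences and no new data, because the flow chart already places a baseline assessment before allocation. With one deciding test the false-positive chance returns to 5% per outcome. Making the unadjusted 6-week t test decisive would also restore 5%. The adjusted comparison is preferred because, at 20 per group and d = 0.8, it has about 73–93% power for correlations of 0.3–0.7, against 69%. The downside is that a significant ANOVA or rank test alone can no longer be claimed.

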In younger people, DRF is mostly associated with fall associated during sports events and road traffic accidents (Burhani and Naqvi, 2020). The incidence of DRF in females is significantly greater than in males incorporating the menopause as responsible factor leading to osteoporosis associated with reduced bone density showing peak between the age group of 60 and 70 (Gutiérrez-Espinoza et al., 2017).

Considering the injury patterns and patient profiles being heterogenous in nature, the management line should prefer the severity of the injury, the desired functional independency of patients along with existing comorbidities. In older adults, the preferred line of management is conservative or non-operative to have good results with foundation stone of immobilisation. Surgical management options include closed reduction and application of a cast, percutaneous K-wires, open reduction and internal fixation with plates, or external fixation according to the patient requirements (Vaghela et al., 2020). Following DRF, many factors manipulate the recovery of the patient implying the age, gender, site and extent of injury, management line followed to manage the respective injury, compensations, patient’s education regarding the condition, radial shortening, and intra-articular involvement (Björk et al., 2020). Patients generally recover within 3-6 months to maximum range of motion, strength and function whether managed conservatively or surgically.

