The Leap Motion Controller is an infrared light detector developed as a means of hand gesture and motion recognition device. The corresponding software applies algorithms to the sensor data detected from the hands and generates a 3D representation of contour, position and movement. Current applications include gaming, education, maps and navigating the computer desktop. The technology lends itself to monitoring hand movement exercises used for wrist physiotherapy. However, no current research exists that investigates the feasibility and validity of using this technology.

**Aim:** To compare the efficacy of leap motion tracking device based rehabilitation and conventional rehabilitation in distal radial fracture patients.

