**Material and Methodology:**

**Study design:** This interventional comparative study will be carried out in the HumEn Research Lab of Ravi Nair Physiotherapy College, Sawangi (Meghe), Wardha, after approval from Institutional Ethics Committee of Datta Meghe Institute of Medical Sciences, Deemed to be University. Before inclusion, all the participants will be informed regarding the aim and procedure of research. Those participants who will meet the inclusion criteria must give the written informed consent. In an experimental study, those participants (N= 40) diagnosed with distal radial fracture will be enrolled for 6 weeks protocol. The participants will be randomly assigned in a 1:1 ratio, a 6-week therapy with leap motion tracking device and a 6-week traditional therapy. Figure 1 shows the flow chart of the study.

**Recruit Subjects(N=40**)

Subjects will be screened by inclusion and exclusion criteria, informed consent & medical history will be obtained from subjects

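### The only follow-up to a significant ANOVA is a within-group t test, which does not compare the treatments, and the plan does not say which analysis decides the trial

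*Protocol*

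**What the plan says.** The aim, at the end of the Introduction, is a comparison of treatments: "To compare the efficacy of leap motion tracking device based rehabilitation and conventional rehabilitation in distal radial fracture patients". Both arms are actively treated for 6 weeks and assessed at baseline and after treatment (Material and Methodology, with its flow chart).

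The Statistical analysis paragraph has three parts:

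- A main model: "To compare the group effect, two-way repeated measures ANOVA (analysis of variance) will be used".
- A follow-up rule: "When ANOVA reveals a significant difference", a Student's "t test will be used to compare the changes within the group". This is the only step tied to the ANOVA result.
- A separate list (t test, Mann-Whitney U or Fisher's exact), which also serves "for comparing the primary and secondary outcomes between the groups at 6 weeks". It does not depend on the ANOVA.

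The threshold is fixed: "Statistical significance is determined by a two-sided p value of less than 0.05". On the expected course, the Introduction says: "Patients generally recover within 3-6 months to maximum range of motion, strength and function whether managed conservatively or surgically".

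**The concern.** A two-way repeated measures ANOVA on two groups and two assessments gives three tests: group, time and group-by-time. The follow-up rule does not say which of them opens it. The time term can be significant simply because patients in both arms recover.

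Whichever term opens it, the rule leads to pre-post tests inside each arm, and these do not address the aim. Significance in both arms says nothing about the device relative to conventional care. Significance in one arm only is not evidence that the arms differ, because the two changes have not been compared with each other.

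At stake is the trial's conclusion. A report that followed this rule could credit the device with ordinary recovery, or present one arm as effective and the other as not when the two are the same.

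**Working it through.** **The plan's own figure.** The Protocol gives no figure for this rule. Its only related calculation is the sample size, for a difference between two independent means. That reproduces: δ = 0.8 × √(20/2) = 2.5298, critical t 0.8512 on 38 df (one-sided α 0.2), power 0.9532, 20 per arm. The trial was therefore sized for a between-group contrast, not a pre-post test.

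**Inputs from the Protocol.** 20 per arm; two-sided 0.05; baseline and post-treatment assessments.

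**Assumptions.** No treatment difference; normal data; the same mean recovery *g* in both arms, in SDs of a single measurement; pre-post correlation ρ. The Protocol gives neither *g* nor ρ, so a range is shown.

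**Step 1. Standardised change.** The SD of a change is √(2(1−ρ)) SDs, so dz = g / √(2(1−ρ)).

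**Step 2. Chance *p* that one arm's paired t test is significant.** Noncentral t with 19 df, critical value 2.093, noncentrality dz × √20.

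**Step 3. Patterns across independent arms.** Both significant: p². Exactly one significant: 2p(1−p).

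| g (SD) | ρ | dz | noncentrality | p | both | exactly one |
|---|---|---|---|---|---|---|
| 0.5 | 0.3 | 0.5/√1.4 = 0.423 | 1.890 | 0.434 | 19% | 49% |
| 0.5 | 0.5 | 0.5/√1.0 = 0.500 | 2.236 | 0.565 | 32% | 49% |
| 0.5 | 0.7 | 0.5/√0.6 = 0.645 | 2.887 | 0.782 | 61% | 34% |
| 1.0 | 0.5 | 1.0/√1.0 = 1.000 | 4.472 | 0.989 | 98% | 2% |

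The two patterns trade off. At dz 0.3, both arms are significant in 6% of trials and exactly one in 37%. At dz 1.5 or more, both are significant in practically every trial.

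**Step 4. Effect of the gate.** The same scenarios were simulated (200,000 trials each), counting exactly one significant arm only when the gating term is also significant.

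| g, ρ | time term significant | group-by-time significant | exactly one, time gate | exactly one, group-by-time gate |
|---|---|---|---|---|
| 0.5, 0.3 | 74% | 5% | 44% | 5% |
| 0.5, 0.5 | 87% | 5% | 47% | 5% |
| 0.5, 0.7 | 98% | 5% | 34% | 4% |
| 1.0, 0.5 | ~100% | 5% | 2% | <1% |

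A time gate barely limits the misleading pattern. A group-by-time gate holds it to about 4 to 5% at 0.5 SD.

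**Step 5. Does naming the group effect settle it?** Not well. With equal baselines and a true difference δ at 6 weeks, the group main effect averages the two assessments: (0 + δ)/2 = δ/2. The group-by-time term carries the full difference in change, δ − 0 = δ.

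**The case against.** The strongest reply is that the treatments are compared elsewhere in the same paragraph. The 6-week between-group tests cover every primary and secondary outcome and do not depend on the ANOVA. The ANOVA is itself introduced as a comparison of the group effect, and it yields a group-by-time term. This stands. A reader might infer that the within-group test replaces the treatment comparison, and the document does not support that.

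Second, the natural reading of the gate may be the group effect named in the sentence before. With identical arms, a group or group-by-time gate opens in about 5% of trials, so a gated one-arm-only result cannot exceed that. This also stands: the 34 to 47% figures apply only if the time term is the trigger. The wording allows that reading but does not require it.

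Third, a reader might take 34 to 49% as the trial's false-positive rate. It is not. The Protocol nowhere makes significance in one arm only a decision rule.

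Fourth, a reader might infer that both arms are bound to show significant improvement. The Introduction gives a 3 to 6 month course with no mean change or SD, and the trial observes 6 weeks of it. The table shows how much depends on that size.

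Finally, within-arm contrasts after a significant interaction are a common simple-effects step, and naming the deciding term could be left to a statistical analysis plan. But the Protocol does not leave the follow-up open. It states a specific step, and that step does not answer the aim. It is harmless only if labelled descriptive, which the Protocol does not do.

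**Conclusion.** The point holds as a misdirected follow-up step and an unclear order among the analyses. The only step attached to a significant ANOVA does not compare the treatments. The between-group tests at 6 weeks do, but they ignore baseline, are left as a choice of three, and are not ranked against the ANOVA.

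The size depends on the assumed recovery, on identical arms with normal data, and on which term opens the gate. A small recovery favours the one-arm-only pattern and a large one favours improvement in both arms. Neither says anything about the device. The sample size calculation is unaffected. Because valid between-group tests are already planned, this is a should-fix, not a fatal fault.

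**What to change.** In Statistical analysis:

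1. Replace the within-group t test as the ANOVA follow-up with the between-group contrast: the 6-week difference adjusted for baseline (or, if the ANOVA is kept, the group-by-time term), with its 95% CI.
2. State that this contrast decides each outcome, and make the other 6-week tests supportive or remove them.
3. Report within-group changes as descriptive only, and say that they are not evidence of a device effect.

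The cost is a few sentences of wording. Baseline and 6-week values are already collected, so no extra patients, visits or measurements are needed.

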**Perform baseline assessment**

**Allocation**

**Control Group**

20 subjects

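### The two planned between-group analyses ignore baseline or use it inefficiently; one ANCOVA per continuous outcome should replace both as the treatment comparison

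*Protocol*

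**What the plan says.** The flow chart under Study design has the step "Perform baseline assessment" ahead of allocation. It does not list the measures taken.

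The Statistical analysis section then names two ways of comparing the groups:

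- First: "To compare the group effect, two-way repeated measures ANOVA (analysis of variance) will be used". If it is significant, t tests of change within each group follow.
- Second: Mann-Whitney U, t-test or Fisher's exact test, for "comparing Groups at baseline and for comparing the primary and secondary outcomes between the groups at 6 weeks".

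It does not say which of the two is the treatment comparison, or whether the ANOVA result of interest is the group-by-time interaction or the group main effect. No model with a baseline covariate appears anywhere in the protocol. The threshold is given as follows: "Statistical significance is determined by a two-sided p value of less than 0.05".

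The sample size section plans 20 per group for an independent two-sample t test with "Effect size d = 0.8", one-sided, and "α err prob = 0.2". It does not say which outcome d refers to, or whether d is on the 6-week or the change scale.

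**The concern.** Baseline DASH, range of motion, grip strength and VAS are not listed in the flow chart. Their collection is nonetheless the natural reading: a repeated measures ANOVA over a 6-week course with one post-treatment assessment needs a pre-treatment value, and the groups are to be compared at baseline.

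Given that, the analyses named make poor use of the data. The rank test and the t test at 6 weeks take no covariate. A separate between-group test at baseline does not adjust the 6-week estimate. With one value before and one after, the ANOVA's group-by-time test is a t test on change scores, which subtracts the whole baseline value whatever its correlation with the outcome. The ANOVA's group main effect averages the 6-week value with a value taken before any treatment, and so dilutes the effect.

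What is at stake is precision in a 40-patient trial whose Power analysis section requires all 20 per group to complete. There is also a practical risk. If a visible baseline gap appears, adjusting for it after seeing the data would be post hoc, and two unranked analyses could disagree.

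**Working it through.** **Inputs.** From the protocol: d = 0.8, n = 20 per group, and two-sided 0.05 from Statistical analysis. Assumed: d is the effect on the 6-week value, variances are equal at baseline and 6 weeks, and the correlation rho between them is 0.3, 0.5 or 0.7.

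**The plan's own figure.** Noncentrality = 0.8 × sqrt(20/2) = 2.5298 on 38 degrees of freedom. At one-sided 0.2 the critical t is 0.8512 and power is 0.9532, which matches the protocol. At the two-sided 0.05 of the analysis section the critical t is 2.0244 and power is 0.693. That drop is a separate issue; 69.3% is the reference here.

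**Effective effect size for each analysis**

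- 6-week t test: d = 0.8, 38 degrees of freedom.
- Group-by-time test (change score): 0.8 / sqrt(2(1 − rho)), 38 degrees of freedom. At rho = 0.5 this is 0.8 / 1 = 0.8, so its power equals that of the 6-week t test.
- Group main effect (mean of the two times): 0.4 / sqrt((1 + rho)/2), 38 degrees of freedom.
- ANCOVA, large-sample: 0.8 / sqrt(1 − rho²), 37 degrees of freedom. At rho = 0.5 this is 0.8 / sqrt(0.75) = 0.924.

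The ANCOVA formula gives 73.3%, 81.2% and 93.2% power at rho 0.3, 0.5 and 0.7. It ignores the cost of estimating the slope, so the table uses simulation for ANCOVA and noncentral-t results for the rest.

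| Assumed rho | 6-week t test | Change score (group-by-time) | Group main effect | ANCOVA (simulated) | Gain over 6-week t test | Gain over change score |
|---|---|---|---|---|---|---|
| 0.3 | 69% | 55% | 33% | 72% | about 3 points | about 17 points |
| 0.5 | 69% | 69% | 30% | 80% | about 11 points | about 11 points |
| 0.7 | 69% | 89% | 27% | 93% | about 23 points | about 4 points |

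**Where ANCOVA stops helping.** With normal data and 38 within-group degrees of freedom for baseline, estimating the slope inflates the variance by 1 + 1/36 = 1.028. ANCOVA therefore beats the 6-week t test when (1 − rho²) × 37/36 < 1, that is when rho > sqrt(1/37) = 0.16. At rho = 0 the simulated variance was 0.1027, against 0.1000 for the t test.

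**Chance imbalance.** The difference in mean baseline has standard error sqrt(2/20) = 0.316 SD, and a gap above 0.3 SD arises in about 34% of such trials. At rho = 0.5 that gap moves the unadjusted 6-week estimate by 0.5 × 0.3 = 0.15 SD, under half that estimate's own standard error of 0.32 SD.

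**The case against.** The strongest reply is that nothing planned here is invalid. Both tests hold their error rate, allocation is random, and the t test's standard error already includes the variation from chance imbalance. That stands: the 34% figure is not a second defect on top of the power loss, and a reader who inferred systematic bias would be wrong. Imbalance adds variance, and error conditional on the gap that occurred.

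A reader might also infer that the plan leaves baseline out altogether. It does not. The repeated measures ANOVA uses it, and is the best evidence that outcomes are measured before allocation. The complaint is about how it is used.

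Nor do the documents support a fixed loss of some 12 points. That is the large-sample formula at rho = 0.5 (11.8 points), and the protocol gives no rho. Simulation puts it at about 11 there, with a range of 3 to 23 over rho 0.3 to 0.7. On the planning basis of one-sided 0.2 the formula gain at rho = 0.5 is only 2.7 points, from 95.3% to 98.1%. The analysis section, however, declares two-sided 0.05, so that is the relevant level.

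It is also too strong to say that ANCOVA is never less precise. That is a large-sample statement, and at 20 per arm it fails slightly below rho of about 0.16.

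Finally, covariate adjustment is often left to a statistical analysis plan, which is not shown. That would answer a silent protocol. This one names its tests, and names two without ranking them.

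**Conclusion.** The point holds as a matter of efficiency and clarity, not validity. The protocol names two between-group analyses for outcomes that are, by clear implication, also measured before allocation. One ignores baseline. The other uses it as a change score or, on the main-effect reading, loses much of the effect.

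The direction is secure for any moderate correlation. The size is not, because it depends on an assumed rho, on reading d = 0.8 as a 6-week effect, and on equal variances at the two times. Which planned analysis loses more also depends on rho: the change score does worse than the 6-week t test below 0.5 and better above it. ANCOVA does better than both across the range shown.

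The change should be made, but it does not repair the larger fall from 95.3% to 69.3% caused by planning at one-sided 0.2 and testing at two-sided 0.05.

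**What to change.** In Statistical analysis, name one ANCOVA per continuous outcome (DASH, each goniometer movement, grip strength, VAS) as the between-group treatment comparison. The 6-week value is the response, group is the factor, and that outcome's own baseline value is the covariate. State that it replaces both the 6-week t test or Mann-Whitney test and the repeated measures ANOVA in that role; changing only the first would leave two competing analyses in place. Report the adjusted mean difference with its 95% confidence interval and two-sided p value. Keep the unadjusted test or the ANOVA as a sensitivity analysis only, and present baseline values descriptively.

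The cost is a few sentences. No new data are needed beyond the baseline assessment already planned, and SPSS fits the model. The downsides are one residual degree of freedom (37 instead of 38), the usual linear-model assumptions, and a negligible loss of precision if rho is below about 0.16.
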